#### Step 3b: Home-based assessment 2 (Confirmed PD only)

Participants from step 3a will be invited to participate in an additional home based assessment to explore the reliability of OMT measurement in PD using the iTremor ONE device. For this, we then visit the participant at the same time as step 3a, one week later. To perform the test re-test reliability, we ask participants to take their medication at the same time as they took it for step 3a. We will collect the following details when ON medication: MoCA, UPDRS-III and OMT (60 minutes after the participant has taken their usual dopaminergic medication).

#### Safety considerations

There are no major disadvantages to participation in this study and no adverse events are anticipated. All measurements are non-invasive and quick meaning the participant is at no/minimal risk, and tasks performed are the same as participants would perform at home/in the community (i.e., no more risk than usual activities). The iTremor device uses optical technology to direct light across the scleral surface (not directly into the eye/pupil) at a safe frequency for use with human eyes, which has been verified by a consultant optical safety expert. Anyone who operates the iTremor device will be trained to do so. The component of the iTremor device that comes into contact with the participants skin is made of silicone and therefore should not cause any harm.

All equipment used with participants will be wiped using iso-propyl 70% alcohol cleaning wipes between each participant to ensure good hygiene. All research equipment (iTremor, inertial sensors etc.) provides no risk of electric shock from electrical failure as the devices are battery powered and therefore low voltage.

### Data analysis

#### Primary outcome

The primary outcome for the study will be frequency (Hz) of OMT, measured via the handheld iTremor device (Head Diagnostics Ltd, Dublin, Ireland). Raw data will be analysed using an algorithm built into the handheld device. Raw data will be securely stored on a removable SD card within the device, which will only be accessed by the investigators.

#### Secondary outcomes

Secondary outcomes for the study include cognition, visual function, motor symptoms (UPDRS-III), gait and balance. Diagnosis will also be recorded from the medical records for Step 1; specifically positive or negative PD diagnosis (i.e., PD; YES or NO).

Within clinic feasibility outcomes will include the following:

The number of adverse events (mild, moderate or severe) during the OMT measurement, if any, are recorded in an incident log. The total number will be assessed and compared.

The number of OMT measurement device issues (e.g., breakdowns, inability to record OMT etc.) and success of data recording (percentage of failed recordings / missing data). This may be device related or due to other factors such as environmental or patient specific difficulties.

Compliance adherence in terms of the number of completed OMT recordings from patients and their timeliness in terms of collection in the patient visit window.

#### Data processing

The study will comply with the General Data Protection Regulation (GDPR) and Data Protection Act 2018, which require data to be de-identified as soon as it is practical to do so. The processing of the personal data of participants will be minimised by making use of a unique participant study number only on all study documents and any electronic database(s). All data samples collected as part of this study will be anonymised with participants being assigned a unique study number (e.g. iTrem_PD_01, iTrem_PD_02 etc.). All data are entered into an electronic database using unique study codes for each participant and are securely stored on a password-protected computer database. We will keep one hard copy of the assessment in locked filing cabinets in the Clinical Gait Laboratory, [name], Northumbria University. This is the only place where we store any personal details like names and addresses. This information is kept locked away and is only available to people directly running the study. These people will treat the information in the strictest confidence.

#### Statistical analysis

Statistical analysis will be undertaken using SPSS version 26 or more recent versions (SPPS, Inc. an IBM company). All statistical tests will be carried out at the 5% two-sided level of significance. Demographic characteristics and baseline data will be summarized using descriptive statistics, including means, standard deviations, median, minimum, maximum and inter-quartile ranges for continuous or ordinal data and percentages for categorical data. The descriptive statistics will be tabulated and presented graphically for clarity.

*Analytical validation aim I*. *Reliability*: To assess test, re-test reliability in PD, OMT frequency outcomes from the iTremor One device will be assessed on two separate home-based sessions and compared. Absolute agreement between sessions will be assessed using intra-class correlations (ICC2,1). ICCs will be interpreted as; poor <0.5, moderate 0.50–0.75, good 0.75–0.90 and excellent >0.90 [49]. Additionally, Bland-Altman graphs, with mean differences and limits of agreement will compare OMT between the two sessions, and Pearson’s correlations will also be used.

*Analytical validation aim II*. *Feasibility*: Feasibility outcomes will also be descriptively reported (e.g., number, percentages etc.) in relation to measurement of the OMT with the iTremor.

*Clinical validation aim I*. *Known groups validity*: To examine whether OMT can differentiate confirmed PD from suspected PD participants, we will use an analysis of variance (ANOVA), with group (confirmed PD vs suspected PD) as a between-subject factor. Although the study is not envisioned or powered to determine the efficacy of the OMT measurement for differential diagnosis of PD, we will further explore the difference in OMT between those with a positive diagnosis and those that did not receive a PD diagnosis. Specifically, receiver operating characteristic (ROC) curve analyses will be used to determine the relative sensitivity and specificity of OMT for differentiating the two patient groups (PD vs other diagnosis). This provides Area Under the Curve (AUC) which is a metric to evaluate the classifiers output quality.

To examine whether OMT can differentiate PD from age-matched controls, we will use an ANOVA, with group (PD vs control) as a between-subject factor. Again, to adjust for covariates (i.e. disease severity/ cognitive function), we will use analysis of covariance (ANCOVA). Receiver operating characteristic (ROC) curve analyses will also be used here to determine the relative sensitivity and specificity of OMT for differentiating People with PD and healthy controls. This provides AUC which is a metric to evaluate the classifiers output quality.

*Clinical validation aim II*. *Convergent / Divergent validity*: Pearson’s correlations will be used to detail the relationships between OMT measurement and other clinically relevant outcome measures, such as the UPDRS or MoCA.

*Clinical validation aim III*. *Known intervention response*: To examine whether OMT reduces when in the OFF-medication state in PD, we will use an ANOVA with medication-state (ON vs OFF medication) as repeated measures.

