**Fig 1 pone.0313452.g001:**
[figure not shown]
SPIRIT diagram, schedule of enrolment and assessments.

#### Step 3a) Home assessment 1

We will recruit 30 people with confirmed PD to participate in a home based assessment.

#### Step 3b) Home assessment 2

We will recruit 20 people with confirmed PD who participated in step 3a to participate in a second re-test home based assessment of reliability.

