*OMT assessment*: OMT will be measured using the iTremor Device (Fig 2). The participant will be asked to sit comfortably with their head resting on the chair’s headrest. If the participant wears glasses or contact lenses they will be asked to remove these for the duration of the recordings. The participant is asked to look straight ahead at a target on the wall without straining their eyes for a ~3 second period. The participant remains relaxed whilst the researcher positions the device, gently leaning on the participants cheek and brow bone. The guide light is lined up from the side of the eye with the scleral surface of the eye and the researcher cues the participant to not blink before pressing the trigger on the device. An optical beam is emitted from a diode in the device at low power with light scattered back from the eye and reflected back into the device and passed to a video imaging sensor. Three readings will be taken for each eye. If the participant blinks, the reading is just repeated. Unwanted eye movements or blinks are filtered out in raw data post-processing. A frequency will be shown on the device’s display screen in Hz. This is repeated three times for each eye independently.

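### With 20 people and two sessions the ICC cannot reliably place reliability in one of two adjacent bands, and no planned reliability analysis separates within-session error from one-week change

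*Protocol article*

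**What the plan says.** The first analytical aim in the Introduction is the test-retest reliability of the handheld device in people with Parkinson's disease. The parts of the plan that bear on it are:

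- **Sample.** The Participants section, under Step 3b, sets the size of the retest group: "We will recruit 20 people with confirmed PD who participated in step 3a to participate in a second re-test home based assessment of reliability".
- **Timing.** Step 3b: Home-based assessment 2: "we then visit the participant at the same time as step 3a, one week later". Medication state is matched: "We will collect the following details when ON medication: MoCA, UPDRS-III and OMT", with OMT taken 60 minutes after the dose.
- **Readings per session.** The OMT assessment under Step 2 specifies three readings per eye: "This is repeated three times for each eye independently". Step 3a uses the same procedure at home.
- **Analysis.** Statistical analysis, Analytical validation aim I: OMT frequency "will be assessed on two separate home-based sessions and compared". The statistic and the first band are given as "Absolute agreement between sessions will be assessed using intra-class correlations (ICC2,1). ICCs will be interpreted as; poor <0.5". The other bands are moderate 0.50–0.75, good 0.75–0.90 and excellent above 0.90. Bland-Altman plots with limits of agreement and Pearson correlations between the sessions are also planned.

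The article mentions no confidence interval for the ICC. It does not say whether a single reading or a session mean enters the ICC, and it gives the repeated readings within a session no role in the reliability analysis.

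**The concern.** Two things limit what the reliability result can tell a reader.

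The first is precision. The bands are 0.25 and 0.15 wide in the range that matters, and an ICC from 20 pairs has an interval wider than either. A single label taken from such an estimate can easily be the neighbouring one.

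The second is interpretation. Two sessions a week apart can disagree because the measurement is noisy or because the participant's OMT changed. The Introduction gives reason to expect real change: it reports OMT as affected by alcohol and caffeine, and it cites mean frequencies of 73.78 Hz in an ON group and 58.88 Hz in an OFF group. A low between-session ICC would not show which source was responsible.

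The Discussion expects this study to supply the first evidence of reliability for a non-invasive handheld OMT device in this population. An over-confident label, or a low ICC blamed on the wrong source, could carry into later work.

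**Working it through.** **Inputs from the protocol article.** n = 20 people and k = 2 sessions (Step 3b). ICC(2,1) with cut-points 0.50, 0.75 and 0.90 (Statistical analysis). Three readings per eye in two eyes, so six per session (Step 2, OMT assessment). The article derives no figure for n = 20, so there is none to reproduce.

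**Assumptions.** Normal data, no systematic shift between sessions, no dropout, and Step 3b readings taken as in Step 2. The expected ICC is not given, so a range is shown.

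**1. Interval for an observed ICC.** For k = 2, F = (1 + r)/(1 − r). The limits are (F_L − 1)/(F_L + 1) and (F_U − 1)/(F_U + 1), where F_L = F / F(0.975; 19, 20) = F / 2.482 and F_U = F × F(0.975; 20, 19) = F × 2.509.

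At r = 0.80, F = 1.80/0.20 = 9.
- F_L = 9/2.482 = 3.626, so the lower limit is 2.626/4.626 = 0.568.
- F_U = 9 × 2.509 = 22.58, so the upper limit is 21.58/23.58 = 0.915.

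The two-way absolute-agreement interval gives the same limits to three decimals. In simulated ICC(2,1) data the typical interval at an observed 0.80 is 0.56 to 0.92.

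| Observed ICC | 95% interval | Bands touched |
|---|---|---|
| 0.70 | 0.39–0.87 | poor, moderate, good |
| 0.75 | 0.48–0.89 | poor, moderate, good |
| 0.80 | 0.57–0.92 | moderate, good, excellent |
| 0.85 | 0.67–0.94 | moderate, good, excellent |
| 0.90 | 0.77–0.96 | good, excellent |

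**2. How often a label from the estimate is wrong.** Simulated ICC(2,1), 100,000 data sets per true value:

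| True ICC | Poor | Moderate | Good | Excellent | Wrong label |
|---|---|---|---|---|---|
| 0.625 | 21% | 64% | 15% | 0% | 36% |
| 0.70 | 9% | 59% | 32% | 1% | 41% |
| 0.80 | 1% | 28% | 66% | 5% | 34% |
| 0.825 | 1% | 19% | 71% | 9% | 29% |
| 0.85 | 0% | 11% | 72% | 17% | 28% |
| 0.95 | 0% | 0% | 6% | 94% | 6% |

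A true value of 0.75 is left out because a value on a cut-point splits about evenly at any sample size. Bands that are far apart do separate: at a true ICC of 0.85 the poor label appears in 0.2% of runs.

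**3. Sources of disagreement.** Split the variance of one reading into person, person-by-day and within-session parts. The single-reading between-session ICC is person/total. The within-session ICC is (person + day)/total. Two illustrative splits, which are assumptions:

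| Person / day / within-session | Between-session ICC, one reading | Within-session ICC | Between-session ICC, mean of six |
|---|---|---|---|
| 0.70 / 0.25 / 0.05 | 0.70 | 0.95 | 0.70/(0.95 + 0.05/6) = 0.73 |
| 0.70 / 0.05 / 0.25 | 0.70 | 0.75 | 0.70/(0.75 + 0.25/6) = 0.88 |

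The single-reading ICC is identical, yet the dominant error source is opposite. The last column treats the six readings as exchangeable. It also shows that the choice between one reading and the mean can move the result from moderate to good.

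**4. Whether the data can separate the sources.** Within-session error has 20 people × 2 sessions × 2 eyes × (3 − 1) = 160 degrees of freedom, so it would be well estimated.

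**The case against.** Several stronger readings are tempting and the article does not support them.

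- **That the label is tied to the point estimate.** The text is silent on intervals and does not exclude them. The full protocol or analysis plan may add one. This stands, so the point is only that the bands appear without an interval.
- **That the ICC is the sole reliability analysis.** It is not. The Bland-Altman limits give between-session disagreement in Hz. Their half-width, 1.96 × SD of the differences, is the usual smallest detectable change, and that SD divided by √2 is the single-session error SD. But the limits also compare sessions a week apart, so they mix the same two sources.
- **That between-session variation does not belong in this aim.** The aim is test-retest reliability, which properly includes it, and it is the relevant error for monitoring. The design also restrains it by matching time of day and dose timing. The separation is needed to interpret the result, not to replace it.
- **That the repeat readings isolate device error.** They do not. The researcher positions the device by hand, so within-session spread includes operator positioning and short-term physiology, while day-specific set-up error falls in the between-session part.
- **That the label should come from the lower confidence limit.** That rule is conservative and debatable. At a true ICC of 0.85 the lower limit reaches 0.75 in about 21% of studies, so a truly good measurement would be denied that label about 79% of the time.

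The study is also an exploratory pilot without a formal sample size calculation, and no success criterion depends on the label. So n = 20 is not a calculation error.

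**Conclusion.** The concern holds in a limited form. With 20 pairs, adjacent bands cannot be told apart reliably: intervals at observed ICCs of 0.70 to 0.85 touch three bands, and labels from the estimate are wrong in about 28% to 41% of studies at the true ICCs examined between 0.625 and 0.85. A reader might infer that the label is mostly chance. The figures do not support that, because most labels are still right, distant bands separate, and a true ICC of 0.95 is labelled correctly about 94% of the time.

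All planned reliability analyses mix within-session measurement error with one-week change. This is a limit of the stated analysis and not of the design, which already collects the repeat readings.

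The interval and labelling figures rest on the assumptions listed above, and dropout would widen every interval. The variance splits are illustrations and not estimates for this device. The point is an inexpensive improvement to an exploratory analysis and does not show an error that invalidates the study.

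**What to change.** In Analytical validation aim I:

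1. Report the ICC with its 95% interval and name every band the interval covers, instead of giving one label from the estimate.
2. State whether a single reading or the session mean enters the ICC.
3. Fit a variance-components model to all readings, with participant, session, eye and replicate as sources. Report the within-session SD and between-session SD in Hz as within-session repeatability and one-week stability, and do not describe the within-session part as pure device error.
4. Keep the Bland-Altman limits as the between-session summary in Hz.

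The cost is a little more analysis and less clear-cut labels. No extra patients, visits or measurements are needed.

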#### Step 2) Lab assessment

We will recruit 30 confirmed PD, 30 suspected PD, and 30 age-matched healthy control participants for laboratory and home-based assessment of OMT (Fig 1). As this is a pilot study of a novel OMT measurement device and we are interested in the feasibility of measuring OMT in a real-world clinic setting rather than determining efficacy of OMT for differential diagnostics in PD within clinical settings, a formal sample size calculation was not conducted. We have based the sample size on previous studies of eye-tracking in PD that have used samples <30 per group and found significant differences compared to controls [34].

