#### Step 2: Laboratory assessment (Suspected PD, confirmed PD and HC groups)

*Demographics*. The participant will then be interviewed by a member of the study team. The interview will include questions regarding education level, falls history, current medications, history of head injury, activity level, and side dominance as well as basic demographics such as age and gender. We will ask participants for their medications currently used (so that we can calculate the levodopa equivalent daily dosage (LEDD) [37, 38].

*Cognitive assessment*: Participants will also undergo a battery of cognitive, motor, and visual assessments. The cognitive assessments should last around 30 minutes and consist of a series of pen and paper tasks which the participants will be guided through by a member of the research team. Global cognition is assessed using the Montreal Cognitive Assessment (MoCA) [39]. Benton’s Judgement of Line Orientation test assesses visuospatial skill (JLO) [40]. The trail making test of visual attention (TMT A and B) is used to assess executive functioning [41] as well as Royall’s Clock Drawing task (CLOX 1&2) [42]. Forward digit span [43] is used as a measure of working memory. Participants will also complete a series of computerised tests to assess attention using a button pressing task. This attention battery is a valid means of testing attention and has been implemented in previous studies involving People with PD [44].

*Visual assessment*: The visual assessments are conducted binocularly before using an eye occluder to measure for the left and right eyes independently. The visual assessments should take 10 minutes to complete.

*Visual acuity—LogMAR*. This test is a simple visual test to assess participants ability to read at a distance. The Logarithm of the Minimal Angle of Resolution (LogMAR) is used as a standardised binocular measure. Participants are seated at a 4-meter distance from the chart and asked to read the letters aloud from left to right starting at the top left. The participant is stopped if two incorrect letters are given. LogMAR is calculated using the following formula: LogMAR = (score of the line before termination)–(0.02 x the number of errors) + (0.02 x correct answers before terminal line). A LogMAR score of 0.00 is equivalent to 6/6 (20/20) vision. The LogMAR charts are scored by letter instead of row making them a more precise measure of visual acuity.

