*Contrast sensitivity—LogCS*. This is measured using the Mars CS sheets. These sheets consist of 48 Latin letters of uniform height, and the contrast from the white background decreases with each letter. The participant is seated 50 centimetres (cm) from the sheet and again reads from left to right, starting at the top left. Errors are recorded by the investigator and the test is terminated when two consecutive errors are made. LogCS is calculated using the following formula: (value of final correct letter before stopping)–(number of errors prior to stopping x 0.04). Again, answers are recorded for binocular vision then for left, and right eyes independently using an occluder.

*Motor assessment*: To assess disease severity and motor symptoms in People with PD, the Movement Disorder Society Unified Parkinson’s disease Rating scale part III (UPDRS-III) is used [45]. The motor assessments should take around 30 minutes. The UPDRS will be conducted first before setting up the sensors for the balance and gait assessments. People with PD will be categorised based on their disease severity using the Hoehn and Yahr scale (H&Y) [46]. This is a widely used clinical scale for defining motor symptoms in PD, which is a part of the UPDRS-III. It consists of five stages–stage I, unilateral symptoms with no functional disability, to stage V, complete disability and patient is bedbound. This scale is easily applicable and widely used to assess PD. There will also be a short self-report questionnaire on freezing of gait, using the new Freezing of Gait Questionnaire (nFOGQ) [47]. In addition, the Falls Efficacy Scale–International (FES-I) [48], a self-report evaluation to assess fear of falling will be completed.

*Balance*. Participants will stand for several periods of up to 2 minutes under different conditions (i.e., eyes open, eyes closed, and on a foam block with eyes open, and closed) with balance measured via mobile inertial measurement units (APDM, USA). These sensors are located at the wrists, feet, chest, and lower back to measure postural sway.

*Gait*. Participants will walk back and forth over a marked out 10m distance for several periods of up to 2 minutes under different conditions (i.e., normal walking and walking while repeating numbers) with gait measured via mobile inertial measurement units (APDM, USA). Turns are included in this walking sequence. These sensors are located at the wrists, feet, chest, and lower back.

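### The PD-versus-control ANCOVA adjusts for disease severity, which is defined only for people with PD, so its group coefficient is either not estimable or not the PD-versus-control difference

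*Protocol article*

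**What the plan says.** For known-groups validity in PD against age-matched controls, the Statistical analysis section states "we will use an ANOVA, with group (PD vs control) as a between-subject factor". The next sentence is "Again, to adjust for covariates (i.e. disease severity/ cognitive function), we will use analysis of covariance (ANCOVA", and the one after it returns to ROC analysis of PD against healthy controls. The covariates are introduced by *i.e.*, so they are the named set and not examples.

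Severity is defined in the Motor assessment part of Step 2. UPDRS-III is used "To assess disease severity and motor symptoms in People with PD", and "People with PD will be categorised based on their disease severity using the Hoehn and Yahr scale (H&Y". The Hoehn and Yahr stages are described as running from stage I, "unilateral symptoms with no functional disability, to stage V, complete disability and patient is bedbound". The text gives no stage or severity value for a person without PD. The heading of that step does, however, cover all three groups: "Laboratory assessment (Suspected PD, confirmed PD and HC groups".

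On size, the Step 2 recruitment text says "We will recruit 30 confirmed PD, 30 suspected PD, and 30 age-matched healthy control participants", and that "a formal sample size calculation was not conducted".

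**The concern.** A covariate in a two-group ANCOVA must have a meaning and a value in both groups. Its distributions should also overlap enough for the groups to be compared at a common value. Disease severity fails this test for PD against healthy controls, because it is a consequence of being in the PD group. Holding it constant asks how OMT would differ between a control and a PD patient with a control's severity. Aim I asks a different question, namely whether OMT differs between people with PD and controls.

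At stake is the only adjusted analysis of the primary outcome stated for this comparison. If controls are scored, the model will run and print a plausible estimate and p-value, so the fault would be easy to miss. An adjusted result much weaker than the unadjusted one could then be misread as evidence against OMT as a marker.

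**Working it through.** The protocol states no power or effect size, so there is no figure of its own to reproduce.

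**Inputs**
- 30 per group (Step 2 recruitment text); 5% two-sided tests (Statistical analysis).
- OMT in the earlier study cited in the Introduction: controls 81.64 Hz (SD 6.10), PD ON 73.78 Hz (SD 5.55). Using the ON figures is an assumption, for scale.
- Severity: the protocol gives no distribution. Assumed UPDRS-III mean 30, SD 10 in PD, and 0 in controls; varied below.

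**Branch A: controls have no severity value.** Listwise deletion leaves only PD participants. The group column then equals the intercept, the design matrix has rank 2 of 3, and the group effect cannot be estimated.

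**Branch B: controls are scored at 0.**

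*Unadjusted.* Difference (PD minus control) = 73.78 - 81.64 = -7.86 Hz. Pooled SD = √((6.10² + 5.55²)/2) = 5.83. SE = 5.83 × √(1/30 + 1/30) = 1.51 Hz. Power is above 99%.

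*Adjusted.* Controls do not vary in severity, so the severity slope *c* comes from the PD group alone: c = r × 5.55/10, where *r* is the OMT-severity correlation within PD. The group coefficient is the PD regression line read at severity 0, minus the control mean:

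b = -7.86 - 30c

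SE = s × √(1/30 + 1/30 + 30²/(29 × 10²)) = s × √(0.0667 + 0.3103) = 0.614 s

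Here s = √((6.10² + 5.55²(1 - r²))/2). The variance inflation is 0.377/0.0667 = 5.7.

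| r within PD | c (Hz per point) | Adjusted difference (Hz) | s | SE (Hz) | Rejection rate, simulated |
|---|---|---|---|---|---|
| 0 | 0 | -7.86 | 5.83 | 3.58 | 57% |
| -0.3 | -0.1665 | -7.86 + 5.00 = -2.9 | 5.71 | 3.51 | 12% |
| -0.5 | -0.2775 | -7.86 + 8.33 = +0.5 | 5.49 | 3.37 | 3% |

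The last column is from simulated regressions (3,000 runs per row), in which the mean SE was 3.4 to 3.7 Hz. If controls instead score about 2 (SD 2), the rates are 63%, 16% and 3%. The adjusted difference is exactly zero when c = -7.86/30 = -0.262, that is r = -0.262 × 10/5.55 = -0.47.

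**Range over other assumed severities.** PD 20 (SD 8), 30 (10) or 40 (12); controls 0, or 2 (SD 2); 1,500 runs each. Variance inflation is 3.7 to 7.2.
- OMT unrelated to severity: difference about -7.9 Hz, SE 2.9 to 4.0 Hz, power 48 to 77%.
- Half of the deficit tracks severity: about -4 Hz, power 18 to 32%.
- All of it tracks severity: about 0 Hz, rejection 4 to 6%, which is about the nominal level.

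**The case against.** **The main comparison is safe.** The unadjusted ANOVA and the ROC analysis are already planned and do not use severity, and nothing says that the adjusted result overrides them. This stands. A reader might infer that the known-groups aim fails as a whole; the protocol does not support that.

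**Controls may well be scored.** Step 2 covers controls, participants in general undergo motor assessment, UPDRS-III is listed as a secondary outcome without restriction, and the schedule in Fig 1 is not shown. So it is not established that the model cannot be fitted. Scoring controls only moves the problem from Branch A to Branch B.

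**The sentence may be misplaced.** It opens with *Again*, yet no ANCOVA precedes it. It may have belonged to confirmed versus suspected PD, where severity could be scored in both groups. That is plausible but unproven, and as printed the sentence governs PD versus control. The argument here does not extend to confirmed versus suspected PD, for which no ANCOVA is stated.

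**The sizes rest on assumed inputs.** This also stands. A reader might infer that the adjusted analysis will probably show no difference. That needs OMT to track severity within PD, which aim II is there to explore. With no such link the estimate is unbiased and, in the main scenario, detection is still more likely than not.

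**An analysis plan could settle it.** The point is not a missing detail: the article names a covariate that does not fit the comparison.

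**Conclusion.** Wrong as written, within a narrow scope. Disease severity is not a valid covariate for PD versus control on either reading of how controls are handled: the group effect is not estimable, or it is an extrapolation to PD with no severity. That conclusion needs only the protocol's own definitions.

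The size needs assumptions. With the cited ON and control values and UPDRS-III mean 30, SD 10 in PD and 0 in controls, the SE more than doubles, from about 1.5 to about 3.5 Hz. The adjusted difference runs from -7.9 Hz (r = 0) through about -3 Hz (r = -0.3) to about 0 (r = -0.5).

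The fault is confined to the severity term in the adjusted analysis. Cognitive function is measured in all Step 2 groups and can remain a covariate.

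**What to change.** In the PD-versus-control paragraph:
- Remove disease severity from the ANCOVA.
- Adjust only for variables defined and measured in both groups, for example age and cognitive function.
- State that the planned unadjusted ANOVA is the main known-groups result.
- Analyse severity within the PD group only, as Clinical validation aim II already does.

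If the sentence was meant for confirmed versus suspected PD, move it to that paragraph and name the covariates for each comparison separately.

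The cost is about one sentence of rewording, with no new data, visits or participants.
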